# Outcome Measures

## Primary outcome

Glycaemic control defined as the change in HbA1c levels at 6-months (and 9-months) compared to baseline levels. HbA1c levels reflect the average glucose level over the past 2-3 months (not influenced by daily fluctuations) and has strong predictive value for diabetes complications^5^.

## Secondary outcomes

The secondary outcome measures at 6-months and 9-months include:

- proportion of participants with good/excellent diabetes control (HbA1c threshold ≤7% & ≤6.5%)
- change in body weight and body mass index
- changes in lipid profile (HDL- and LDL-cholesterol) and blood pressure
- proportion of participants requiring initiation of additional medication or higher dose adjustment for glycaemic control
- proportion of smokers quitting
- change in level of physical activity (step count)
- change in health care attendances and admissions

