## Secondary objectives

- To examine the sustainability of glycaemic control at 9-months following the withdrawal of incentives for people with newly diagnosed type 2 diabetes.
- To study the effect of incentives based on behavioural economic principles on other health indicators including lipid profile, body weight/BMI, blood pressure, diet, physical activity, smoking, and delay of diabetes for people with newly diagnosed type 2 diabetes.

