# Study Design

This study is a randomized controlled trial in adults aged 30-70 (at enrolment) with newly diagnosed type 2 diabetes over the study period of Jan 2020 to Dec 2022. We plan to enrol 261 adults and follow them for 9-months (6-month intervention period and a 3-month post-intervention follow-up period) to assess glycaemic control and other health indicators. A meta-analyses of clinical trials show a pooled difference of -0.6 percentage points in HbA1c after a minimum 8-12 weeks of exercise intervention ^12,13^. Consequently, the 6-month intervention period is designed to be sufficient to assess changes in lifestyle, but not of excess duration in order to reduce participant drop-out and loss to follow-up. If a 6-month trial of lifestyle intervention fails to adequately control blood glucose level, it may be appropriate to consider additional medication for glycaemic control ^4–6^.

Participants will be randomly assigned to one of three groups (in ratio 1:1:1): arm A (financial incentives in addition to standard care), arm B (financial and social incentives in addition to standard care), and arm C (control arm receiving standard care). All participants will establish a baseline step count of physical activity using the second week of recorded measurements. The first week of recorded measurements will be ignored to minimise the potential upward bias from elevated physical activity during initial device use. Subsequently, all participants will receive weekly increases of 1,000 daily step targets from their baseline levels to a maximum target of 10,000 steps per day (depending on age, physical condition, physician guidance). The 10,000-step target approximates the 30 minutes of daily exercise recommended by the American College of Sports Medicine ^14^. We will impute daily values less than 1,000 steps as these values are unlikely to represent actual activity ^15,16^. Participants will use their smartphones to track step counts on the same pre-specified activity tracking app for consistency. Although smartphones are expensive, smartphone penetration in Hong Kong is very high, at above 88% of the population aged 10 or above in 2017 ^17^. All participants will be provided with a pedometer to account for physical activity. Participants are followed for an additional 3-months after the cessation of incentives to assess any continued effects and the sustainability of lifestyle change.

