## Incentives

Incentives will be provided in this study to compensate participants for their time, inconvenience, and discomfort, which is standard research practice for studies of this nature, and we believe is necessary to maintain participation. All participants will be offered an incentive of free basic blood tests including glucose control and cholesterol at enrolment (if no contemporaneous results), 6-months and 9-months. Laboratory test results will be given back to each participant. If a result falls out of its reference range, our research team will advise the participant to seek medical consultation for further assessment. All participants will also be provided with a pedometer to track their physical activity. In addition, they will be offered an incentive of a gift voucher valued at HKD 50 gift coupon upon: (1) completion of study enrolment and (2) completion of the study. Participants in the two intervention groups will receive up to HKD 1,000 cash as the intervention being administered.

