## Medications permitted and not permitted before and/or during the study

Participants eligible for the study must be newly diagnosed with diabetes within a year. Participants can continue taking other medication, treatment or routine for conditions other than diabetes should they be enrolled at any time of the study. Participants are allowed to initiate additional medication for glycaemic control during the 6-month follow-up period, and other medication including agents to control lipid levels or blood pressure. The inclusion criteria of HbA1c ≤ 9% is in accordance with the Hong Kong reference framework for diabetes care recommendation of insulin for HbA1c > 9%^5^.

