# Statistical analysis

## Statistical methods

We compare sample characteristics between the arms using ANOVA for continuous variables, and Kruskal-Wallis test for categorical variables. The change from baseline HbA1c will be calculated for each individual participant. The time-matched change from baseline data will be analysed by a repeated-measure analysis of covariance (ANCOVA), fitting terms appropriate to the study design, including treatment group, time and group-by-time interaction. Participants will be included in the model as a random effect. Baseline values will be included as a covariate in the above models. Interim analysis will be performed after ~50% participants having completed the study. We will use the bootstrap method to resample participant groups 200 times to calculate the 95% confidence intervals. As a sensitivity analysis, we will use per protocol analysis to check for the robustness of our results. All analyses will be conducted using R statistical software.

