## Procedure for accounting for any missing data

If missing data are present in the computerized database, we will first check the original records to attempt to complete those variables. In the analyses, we will use multiple imputation^26^ with 10 imputed datasets to replace missing values on outcome and predictor variables (using the *mice*/*Hmisc* package in R) and combine the results using Rubin’s rules^27^. If 10 imputed datasets are not sufficient to ensure stability of estimates, we will use 20 imputed datasets. The imputation predictors will include HbA1c at baseline, 6-months and 9-months; weight; age; and sex. Multiple imputation makes maximum use of available data and maximizes statistical power while requiring less strict theoretical assumptions than to a complete case analysis, or single imputation of mean values; this is a standard method for analysing clinical trials data ^28^.

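### The listed imputation predictors leave out study arm, so imputed HbA1c values pull every arm contrast, including the primary one, toward zero

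*Protocol*

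**What the plan says.** Protocol, Procedure for accounting for any missing data: missing values on outcomes and predictors are to be replaced by multiple imputation with 10 datasets (20 if estimates are unstable) and combined by Rubin's rules. The model inputs are named: "The imputation predictors will include HbA1c at baseline, 6-months and 9-months; weight; age; and sex".

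Protocol, Statistical methods: change in HbA1c is analysed by a repeated-measures ANCOVA with treatment group, time, their interaction and baseline, and a random participant effect.

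Protocol, Selection of participants to be included in the analyses: intention to treat, with everyone randomised.

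Protocol, Secondary outcomes: the list includes the "proportion of participants with good/excellent diabetes control" at HbA1c cut-offs of 7% and 6.5%, which are computed from the same HbA1c values. Secondary objectives adds "To examine the sustainability of glycaemic control at 9-months following the withdrawal of incentives", which also relies on HbA1c at a visit where some values will be missing.

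**The concern.** An imputation model should contain at least the terms of the analysis that follows it. Here the term of interest, treatment group, is in the analysis model but not among the imputation inputs. A model without arm draws missing values as if the arms did not differ, given the listed variables. The draws are then analysed as if they were data from each arm, and they dilute the difference that the trial is meant to estimate.

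Because everyone randomised is analysed, imputed values enter the primary comparison as well as the threshold outcomes and the 9-month comparison. The protocol justifies imputation partly by statistical power. An imputation that shrinks the effect works against that purpose. With values missing completely at random, leaving out participants who have no follow-up HbA1c would not cause this bias; imputing them without arm would.

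**Working it through.** **Inputs**
- Planned difference -0.6 and SD 1.5 percentage points (Sample size justification).
- 87 per arm, 1:1:1 (Randomization; Sample size justification).
- Missing fraction m. The sample size section inflates 78 per group for 10% dropout: 78 / 0.90 = 86.7, rounded up to 87, which reproduces the plan's figure. This leaves 87 - 78 = 9 lost per arm, m = 9/87 = 0.103. The flow diagram (Figure 1) shows 13 discontinued or lost per arm, m = 13/87 = 0.149. Both are used as a range.
- Assumptions: both incentive arms have a true effect of -0.6; the same m applies in each arm; values are missing completely at random; those missing have neither follow-up HbA1c.

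**Step 1: what the model predicts without arm.** Take the control mean as 0 and each incentive mean as -0.6. Pooled over three equal arms, the expected imputed value given baseline is (0 - 0.6 - 0.6)/3 = -0.4, in every arm.

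**Step 2: arm means after imputation**
- Control: (1 - m) x 0 + m x (-0.4)
- Incentive: (1 - m) x (-0.6) + m x (-0.4)
- Difference: (1 - m) x (-0.6). The imputed part cancels.

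**Step 3: numbers**

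| Missing both follow-up values, per arm | m | Contrast without arm | Shrinkage |
| --- | --- | --- | --- |
| 9 of 87 | 0.103 | -0.6 x 0.897 = -0.54 | 10.3% |
| 13 of 87 | 0.149 | -0.6 x 0.851 = -0.51 | 14.9% |

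**Step 4: simulation check.** 87 per arm, SD 1.5, both incentive arms at -0.6, imputation of one follow-up value from baseline HbA1c, 10 imputations, 1,500 runs.

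| Missing | Imputed without arm | Imputed with arm |
| --- | --- | --- |
| 10% | -0.54 | -0.60 |
| 15% | -0.52 | -0.60 |
| 20% | -0.48 | -0.60 |

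The Monte Carlo standard error is about 0.006 throughout. A second simulation (3,000 runs) gave -0.53 and -0.51 without arm at 9/87 and 13/87, and -0.60 with arm in both.

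**Step 5: one follow-up value observed.** The observed HbA1c carries part of the arm difference into the imputed one. If the effect is similar at both visits and the observed value has coefficient b in the imputation model, the imputed difference is about b x (-0.6) instead of 0, so these participants contribute less shrinkage. The protocol gives no figure for b or for the pattern of missingness. The range is therefore 0 to about 15%.

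**The case against.** The strongest defence is that the word include need not mean include only. The analysis model names treatment group, and a statistical analysis plan that is not shown could add arm to the imputation. That stands as a reason for caution about what will be done. It does not rescue the text, which goes to the trouble of naming the predictors and leaves out the one that matters most for the comparison.

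The size can also be disputed. The 10% covers people who do not complete the intervention as well as those lost to follow-up, and the 13 likewise combines discontinued and lost. Some of these may still give blood. Weight, if measured at follow-up, may carry some information about arm. All of this reduces the shrinkage, and -0.54 and -0.51 should be read as the far end for those counts, not as forecasts. That the bias is toward no difference does not make it harmless in a trial designed to detect one.

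A reader might also infer something stronger: that the threshold outcomes and the sustainability objective are unsound because they count control achieved by drugs. The protocol says "Participants are allowed to initiate additional medication for glycaemic control during the 6-month follow-up period". It foresees that if six months of lifestyle change "fails to adequately control blood glucose level, it may be appropriate to consider additional medication for glycaemic control", and in all arms it tells participants: "If a result falls out of its reference range, our research team will advise the participant to seek medical consultation for further assessment". The document does not support calling this an error:
- The thresholds are clearly defined. Intensification is an outcome of its own, "proportion of participants requiring initiation of additional medication or higher dose adjustment for glycaemic control", at 6 and 9 months, and medication use is recorded at follow-up, so the two can be cross-tabulated.
- The design is declared pragmatic, and the sustainability objective does not ask for control without drugs.
- The protocol gives no intensification rates or drug effects. If 50% are at target and 20% intensified in each arm, the difference in control without intensification could lie anywhere from -20 to +20 points. That is a worst-case bound on assumed rates. In an assumed scenario with 35% intensified in control against 15% with incentives and a drug effect of -1.0, the difference in the share at or below 7% moved only from 20.7 to 18.8 points.
- The per-protocol sensitivity analysis ("As a sensitivity analysis, we will use per protocol analysis to check for the robustness of our results") is not defined here, but its definition can be left to the analysis plan.

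**Conclusion.** The point holds for the imputation model. Followed as written, the predictor list shrinks arm contrasts that use imputed HbA1c, including the primary one, by up to about the fraction of participants with no follow-up HbA1c: from -0.6 to about -0.54 at 9/87 or about -0.51 at 13/87. This rests on data missing completely at random, equal missingness across arms and both incentive arms at the planned effect. Shrinkage is less where one follow-up value is observed and the effect is similar at both visits; the size in other patterns was not derived. The bias is modest, its direction in the case worked is toward no difference, and it is entirely avoidable.

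The treatment of glucose-lowering drugs is a legitimate choice for a pragmatic trial and is not a fault in the plan. An analysis of control without intensification would be an optional addition.

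**What to change.** In Procedure for accounting for any missing data, add study arm (three levels) to the listed imputation predictors, or state that imputation is done separately within each arm. With HbA1c at baseline, 6 and 9 months as separate variables, arm in the equation for each visit lets the arm effect differ by visit, which matches the group-by-time term of the analysis model.

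The cost is a few words in the protocol and one more variable in the imputation call. A masked arm code is enough, so analysis staff can stay blinded. Treatment, visits, sample size, outcome definitions and the primary analysis model do not change.

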## Methods for assessing and analysing of efficacy parameters

Blood samples at baseline, 6-months and 9-months will be tested at an accredited laboratory for blood glucose (fasting glucose, HbA1c), lipid profile (total cholesterol, LDL-cholesterol, HDL-cholesterol, triglycerides), routine blood profile (blood cell counts) and urine cotinine (if smoker).

For objective measurement of step counts, all participants will receive a pedometer to account for physical activity not measured by the smartphone (e.g. when smartphone left on a table). Although smartphones are expensive, smartphone penetration in Hong Kong is very high, at above 88% of the population aged 10 or above in 2017 ^17^. Participants will use their smartphones to track step counts using the same pre-specified activity tracking app to ensure consistency.

Health-related physical activity (Metabolic Equivalent of Task/MET-minutes per week) will be also assessed using participant responses to the validated International Physical Activity Questionnaires (IPAQ)^24^. Adherence to physical activity targets is measured as the mean proportion of participant-weeks achieving their weekly physical activity goals based on step counts. Measurements may also be compared to results from their usual diabetes clinic visits (if any). We will administer EQ-5D questionnaires to measure the health status of the participants and quality of life ^25^, and food frequency questionnaire to evaluate the diet of patients. Surveys will be administered at enrolment, 6-months and 9-months.

# Assessment of Safety

Participants should report any adverse events to the study co-ordinator (contact details are provided to participants). Given the non-clinical nature of the intervention, we do not anticipate any occurrence of SAEs within our study. We will survey participants for any safety issues at 6-months and 9-months after enrolment. We will record and inform the IRB of any reported adverse events. For stopping rule, refer to section 6.2 for details. All trial-related activities including enrolment and follow-up will be conducted by our delegated research team members from the School of Public Health, the University of Hong Kong.

# Statistical analysis

## Statistical methods

We compare sample characteristics between the arms using ANOVA for continuous variables, and Kruskal-Wallis test for categorical variables. The change from baseline HbA1c will be calculated for each individual participant. The time-matched change from baseline data will be analysed by a repeated-measure analysis of covariance (ANCOVA), fitting terms appropriate to the study design, including treatment group, time and group-by-time interaction. Participants will be included in the model as a random effect. Baseline values will be included as a covariate in the above models. Interim analysis will be performed after ~50% participants having completed the study. We will use the bootstrap method to resample participant groups 200 times to calculate the 95% confidence intervals. As a sensitivity analysis, we will use per protocol analysis to check for the robustness of our results. All analyses will be conducted using R statistical software.

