## Randomization

The random allocation process will be concealed from the front-line team, using tamper-proof methods, by way of pre-assignment based on a computer-generated sequence of random numbers administered by an independent research assistant. A sequence of random numbers will be generated prior to the start of the study by a statistician. To avoid baseline unbalance, we will stratify the randomization by age (30-49, 50-70) and sex. Computer software (R) will be used to generate the randomization sequence, using a block randomization structure with block sizes of 6 for the enrolment of participants.

The study will remain blind to laboratory and analysis staff. Research staff members at the designated study clinics who had no access to the randomization sequence will allocate a unique code to each of the participants based on their order of attendance. Because the allocation process will be concealed, the identity of the intervention groups will be unknown to the laboratory staff. The randomization codes will be masked from those assessing the outcomes and will only be revealed to the investigators after completion of the follow-up. A study statistician, uninvolved with other trial activities, will have access to the randomization codes for the purpose of conducting regular interim analyses and safety monitoring.

We will enrol 261 participants and randomly allocate each participant to one of the three study arms in equal proportion (1:1:1 ratio) (Figure 1). We assume 10% of participants do not complete the intervention or are lost to follow-up.

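### Randomisation is stratified by age group and sex, but the primary ANCOVA does not name them as terms; if they are left out and are prognostic, inference is conservative and a little power is lost

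*Protocol*

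**What the plan says.** The Protocol's Randomization section restricts the allocation: "we will stratify the randomization by age (30-49, 50-70) and sex", "using a block randomization structure with block sizes of 6 for the enrolment of participants", to three arms in equal proportion. Two binary factors make four strata.

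The Statistical methods section sets out the repeated-measures ANCOVA for change in HbA1c. Its terms are introduced as "fitting terms appropriate to the study design, including treatment group, time and group-by-time interaction". It then adds "Participants will be included in the model as a random effect" and "Baseline values will be included as a covariate in the above models". No other covariate is named. On intervals it says "We will use the bootstrap method to resample participant groups 200 times to calculate the 95% confidence intervals", without saying whether the resampling keeps to the strata.

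Age and sex do appear in the section on missing data, but only as predictors in the imputation model.

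**The concern.** Stratified blocks force the arms to be nearly balanced on age group and sex. If those factors predict the outcome, the true variance of the arm difference falls. A model without them does not register the fall: their variance stays in the residual, and the reported standard error is that of an unstratified trial. Tests then reject less often than their nominal level, and the precision bought by the design is not used.

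What is at stake is some power in the primary comparison, and a primary model whose covariates a reader cannot fully determine from the Protocol. The validity of the result is not at stake, because the error is on the conservative side.

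**Working it through.** **Inputs from the Protocol (Sample size justification).** Difference 0.6, SD 1.5 in each group, 78 per group, significance level 0.05, equal-variance t-test, 80% power, 10% dropout giving 87 per group.

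**The plan's own figure.** The standardised difference is 0.6/1.5 = 0.40. With a one-sided 0.05 test, 78 per group gives 80.3% power (normal approximation), and the t-test solution is 77.97, so the stated 78 reproduces. With a two-sided 0.05 test, power at 78 is 70.5% (normal) or 69.9% (t), and 80% needs 99 (normal) or 100 (t) per group. For dropout, 78/0.9 = 86.7, so 87 per group and 261 in all, as stated. The two-sided comparison at 78 per group is used below.

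**Assumption.** R² is the share of outcome variance, given baseline, that age group and sex explain. The documents give no value, so 0%, 2%, 5% and 10% are shown. The planning SD of 1.5 is taken as the SD given baseline, which the Protocol does not say.

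**Formulas, with the factors perfectly balanced.**

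- Reported SE without the factors: 1.5 × √(2/78) = 0.240, whatever R² is.
- True SE, and reported SE with the factors: 0.240 × √(1−R²).
- Type I error without the factors: 2(1 − Φ(1.96/√(1−R²))).
- Standardised effect: 0.6/0.2402 = 2.498.
- Power without the factors: Φ((2.498 − 1.96)/√(1−R²)).
- Power with the factors: Φ(2.498/√(1−R²) − 1.96).

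Power without the factors also rises slightly with R², because stratification reduces the true variance whether or not the model uses it. Holding it fixed at 69.9% would overstate the gain: at R² = 10% the t-test power with the factors is 74.4%, which would suggest 4.5 points.

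| R² | SE ratio, without/with | Type I error without | Power without | Power with | Gain (points) |
| --- | --- | --- | --- | --- | --- |
| 0% | 1.00 | 5.0% | 70.5% | 70.5% | 0 |
| 2% | 1.01 | 4.8% | 70.7% | 71.3% | 0.7 |
| 5% | 1.03 | 4.4% | 71.0% | 72.7% | 1.7 |
| 10% | 1.05 | 3.9% | 71.5% | 75.0% | 3.5 |

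**Simulation.** Stratified blocks of 6, four equally likely strata, 234 participants in three arms, one pairwise comparison at a single time point, 6,000 runs per setting:

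| R² | Mean SE without / with | Type I error without / with | Power without / with |
| --- | --- | --- | --- |
| 0% | 0.240 / 0.240 | 4.7% / 4.7% | 70.2% / 70.2% |
| 2% | 0.240 / 0.237 | 5.0% / 5.2% | 70.0% / 70.7% |
| 5% | 0.240 / 0.234 | 4.8% / 5.4% | 69.4% / 71.3% |
| 10% | 0.240 / 0.227 | 4.0% / 5.1% | 70.7% / 74.3% |

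SEs are averaged over the runs with a true difference of 0.6. Monte Carlo error is about 0.6 points for power (√(0.7 × 0.3/6000)) and 0.3 points for type I error (√(0.05 × 0.95/6000)), so the departures from 5% with the factors in are noise. The simulated gains of 0.7, 1.9 and 3.6 points agree with the formulas. The simulation does not fit the full repeated-measures model, so it shows direction and order of size only.

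**The case against.** The strongest reply is that the Protocol never says the factors are left out. Its terms are those appropriate to the design, and stratification is part of the design. A reader might infer from the named terms that age group and sex are excluded and that the trial will therefore report inflated standard errors. The text does not support that: it is silent. A statistical analysis plan, if there is one, may name them. This stands, and it limits the point to what the Protocol leaves open. It does not remove the point. The Protocol goes on to name the random effect and the baseline covariate, so an analyst working from it could fit exactly those terms. The open wording also does not say whether age would enter as two groups or as a continuous variable.

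Second, the harm is conditional and small. This also stands. No section says that age group or sex predicts HbA1c change once baseline is in the model, and at R² = 0 nothing is lost.

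Third, the planned 95% intervals come from a bootstrap, so model-based standard errors do not fix their width. A reader might infer that the published intervals will be too wide; that is not shown, because the resampling scheme is not described. Nor does the bootstrap settle the matter. Resampling participants without regard to stratum, around a model without the factors, would not recover the gain from stratification.

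Fourth, the two-sided power of about 70% at the planned size might be blamed on the missing covariates. It is a separate matter: the stated 78 per group reproduces only with a one-sided test.

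Finally, several secondary outcomes are proportions. In a logistic model, added covariates change the odds ratio from marginal to conditional, and the estimates may be unstable among the few smokers. This stands, so the recommendation stops at the continuous outcomes.

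**Conclusion.** The point holds in a limited form. The Protocol randomises within age group and sex but does not state that the primary model includes them. A model built from the named terms alone would be conservative if the factors are prognostic beyond baseline. For an assumed R² of 2%, 5% and 10%, the power forgone at 78 per group, two-sided, is about 1, 2 and 3.6 points, and the type I error is about 4.8%, 4.4% and 3.9% instead of 5%. At R² = 0 there is no effect. There is no bias and no excess of false positives at any value.

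These figures rest on the assumed R² range, on 1.5 as the SD given baseline, and on a single pairwise comparison. This is a nearly free improvement to the plan and not a threat to its conclusions.

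**What to change.** In Statistical methods, name age group (30-49, 50-70) and sex as fixed effects in the primary repeated-measures ANCOVA, alongside baseline. Do the same in the models for the continuous secondary outcomes: weight and body mass index, lipids, blood pressure and step count. Do not extend this automatically to the outcomes that are proportions.

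State also that the bootstrap resamples participants within arm and stratum, so that the intervals reflect the design.

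The cost is a sentence or two and two degrees of freedom. If the factors prove not to be prognostic, almost nothing is lost: simulated power is 70.2% either way.
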